## Abstract

Telehealth and remote monitoring are increasingly used in the management of long-term health conditions and can improve access to care. The Mersey Care Telehealth Service (MCTS) provides technology-enabled support for people with heart failure, diabetes, and chronic obstructive pulmonary disease. The service has been operating for over a decade; however, the COVID-19 pandemic has led to its rapid expansion. This study aims to gather evidence on the impact of the MCTS, explore barriers and enablers to effective service delivery and evaluate its cost-effectiveness. This study comprises of four work packages (WP). WP1: A retrospective observational analysis to evaluate whether the MCTS is associated with reduced unplanned healthcare utilisation and to examine how outcomes vary by sociodemographic characteristics and service delivery type; WP2: Longitudinal analyses to compare patient-reported outcomes, including mental health, quality of life, and wellbeing, between telehealth users and a comparator group of non-users who meet the eligibility criteria for telehealth; WP3: Remote semi-structured interviews with MCTS staff and patients will be held to explore the barriers and enablers influencing the effective service delivery; WP4: An economic evaluation will determine whether the MCTS is cost-effective compared with usual care, and will assess how cost-effectiveness varies by patient characteristics and service delivery type. This multi-method evaluation will provide robust and comprehensive evidence of the impact, equitable delivery, implementation approach, and cost-effectiveness of the MCTS. Insights seek to inform service improvement, commissioning decisions, and future telehealth strategy within the NHS.

## Introduction

Digital health technologies now form an essential pillar of modern healthcare delivery, rather than merely auxiliary tools. Within the United Kingdom (UK), remote monitoring and digital-first strategies are at the forefront of National Health Service (NHS) transformation thanks to national policy drivers like the NHS Long Term Plan (Department of Health and Social Care 2025, NHS 2019), Data Saves Lives (Department of Health & Social Care, 2022), and A Plan for Digital Health and Social Care (NHS England, 2019a; Department of Health & Social Care, 2022). Recent government and NHS policies focus on virtual care, remote monitoring (NHS England, 2025a), digital-first primary care (NHS England, 2019a), interoperability (NHS England, 2025b), and making it easier for people to get health information (Department of Health & Social Care, 2022). The recent NHS 10-Year Plan focusses on moving towards more preventative, digitally enabled services that are closer to home (Department of Health and Social Care, 2025). Digital communication and tools support synchronous (where patient data are reviewed remotely), asynchronous (where clinicians contact patients directly when assessment is required), and mixed-modality (integrating both asynchronous monitoring and synchronous clinical support) approaches to healthcare provision. The descriptions are often used interchangeably; however, they are conceptually different (Van Dyk, 2014). Telehealth refers to the use of digital and communication technologies to support health-related assessment, monitoring, education, self-management, and clinical decision-making at a distance, i.e., at the patients’ home (Van Dyk, 2014). Telemedicine typically describes synchronous consultations provided remotely rather than in person (Choudhury et al., 2022; Yadav et al., 2022); telemonitoring relates to the provision of home monitoring services, to collect health measurements, and/or structured remote (e.g., telephone) support (Scholte et al., 2023); Telecare refers to services typically provided to older adults with social care needs and can include monitoring of both health and behavioural factors (e.g., eating/drinking or falls) (Lassar and Hertelendy, 2024). Virtual clinics are pre-booked synchronous appointments that either replace or supplement out-patient care (Vashishth et al., 2026). Virtual wards deliver short-term, intensive, hospital-standard care to patients remotely in their own homes (Alhakem et al., 2025).

Telehealth is an important part of proactive management of health conditions and making care more accessible, which helps the NHS reach its goals of prevention, efficiency, and fair access. By enabling remote monitoring and care, it can help reduce pressure on NHS and social care services, improve multidisciplinary working, and enhance patient safety, particularly for remote or vulnerable populations. Although early uptake was variable, telehealth adoption increased substantially following the COVID-19 pandemic, aligning with the NHS England’s strategy to expand technology-enabled care and transform healthcare delivery (Department of Health & Social Care, 2022; NHS England, 2023).

### Evidence for telehealth in chronic disease management

Telehealth interventions are implemented across different stages of the chronic disease pathway, serving distinct purposes. The evidence base for digitally enabled care in long-term conditions is heterogeneous, partly because interventions are implemented at different stages of the patient pathway. Some interventions support early identification and risk stratification, while others focus on medication optimisation, routine follow-up, self-management support, early deterioration detection, or long-term disease management. In diabetes, for example, digital interventions support blood glucose monitoring, medication titration, lifestyle coaching, structured education, complication screening, and routine review. In chronic obstructive pulmonary disease (COPD) and heart failure (HF), remote monitoring focuses more directly on the early detection of deterioration, support for self-management, reduction of avoidable face-to-face contact, and timely escalation of care before crisis presentation. The Mersey Care Telehealth Service (MCTS) most closely aligns with clinician-led management of long-term conditions and the early detection of deterioration. In addition, it supports patient education and care coordination, rather than operating solely as a screening, appointment-based, or educational digital intervention.

There is evidence to support telehealth care for the management of HF (Pandor et al., 2013), COPD (McLean et al., 2011), and diabetes (Mabeza et al., 2022). For example, a systematic review identified five studies evaluating the impact of synchronous primary care telemedicine (i.e., real-time remote consultations) compared with in-person visits on diabetes outcomes. (Mabeza et al., 2022). Three studies included control groups following usual care with in-person visits. They showed that telemedicine led to significantly greater glycohemoglobin (HbA1c) reduction over 6 months, with similar or better HbA1c outcomes at 12 months. The other two studies showed improved HbA1c levels with telehealth but did not include comparisons with usual care. A UK randomised controlled study (Basudev et al., 2016) showed equivalent glycaemic control between the virtual clinic and standard care groups. However, the study was limited to six general practices in South London, which lacked established integrated telehealth service. The 2011 Cochrane systematic review of telehealth care for COPD found that telehealth care was associated with lower odds of emergency attendance over 12 months (OR 0.27, 95% CI 0.11–0.66, 3 trials, *n* = 449), and lower odds of hospital admission over 12 months (OR 0.46, 95% CI 0.33–0.65, 6 trials, *n* = 604) (McLean et al., 2011). There was no significant difference in 1-year mortality. Telehealth care was related to a better quality of life recorded by the St George’s Respiratory Questionnaire (two trials, *n* = 253, mean difference − 6.57, 95% CI –13.62–0.48 with minimum clinically significant difference being a change of −4.0). However, health economic evaluations remain scarce, and robust post-COVID-19 evidence is still lacking.

Evidence on whether telehealth care can reduce demand for urgent and emergency services is inconsistent (Janjua et al., 2021; McLean et al., 2010). A recent systematic review of remote monitoring in COPD included 29 studies (5,654 participants), but the studies were at high risk of bias, the certainty of evidence ranged from moderate to very low (Janjua et al., 2021). Early pre-pandemic evaluation of the Mersey Care (MC) model in the Liverpool area of Cheshire and Merseyside showed a small reduction in the use of emergency care services (the average treatment effect was 0.08 [95% CI, 0.05–0.11], corresponding to an average percentage decrease of 22.7%) (Van Berkel et al., 2019). Often health outcomes are unaffected by an intervention, findings show services producing small benefits for increased costs (Salisbury et al., 2017). Previous telehealth evaluations have often been limited by small pilot samples, short intervention periods, and insufficiently established services. Many studies also lack methodological rigour, including appropriate control groups and cost-effectiveness analyses. Importantly, few have examined differential effects across socioeconomic or patient groups, limiting evidence on telehealth’s potential to reduce health inequalities (Salisbury et al., 2017).

### The impact of COVID-19 on telehealth adoption

Although a substantial body of literature has examined the rapid expansion of telehealth during and following the COVID-19 pandemic, important evidence gaps remain. Existing studies have frequently focused on single clinical conditions, individual technologies, or narrowly defined outcomes. In contrast, relatively few studies have evaluated large-scale, routine telehealth services operating across multiple long-term conditions while simultaneously examining healthcare utilisation, patient-reported outcomes, health inequalities, implementation processes, and economic outcomes (Gajarawala and Pelkowski, 2021; Hanlon et al., 2017; Moynihan et al., 2021). Additionally, concerns regarding digital exclusion and unequal access to telehealth persist, particularly among socioeconomically disadvantaged and digitally underserved populations (Shaw et al., 2021; Williams and Shang, 2024). The need for robust evaluations of integrated telehealth programmes has therefore been highlighted by both NHS policy and digital health evidence frameworks (NHS, 2019; National Institute for Health and Care Excellence, 2022; NHS England, 2019b).

Healthcare services are experiencing unprecedented pressures, especially services in areas of high deprivation such as MC NHS Foundation Trust. Since 2011, MC has successfully implemented telehealth services for patients with long-term physical health conditions, particularly during the pandemic and amid increasing fiscal pressures on the NHS. Now, the Trust is considering extending telehealth to mental health services in line with NHS priorities (NHS England, 2023; 2024a). This study seeks to address important evidence gaps regarding the impact and cost-effectiveness of telehealth, particularly for marginalised and underserved populations. The initiative aims to improve patient outcomes, reduce health inequalities, and support healthcare professionals in managing workload demands, while generating critical evidence for the NHS on the overall impact of telehealth, service utilisation, and equitable access to care. Through this research, we aim to develop a comprehensive understanding of telehealth delivery and outcomes that can inform future service development, adaptation, and scale-up. Accordingly, the study is organised into four work packages (WPs):

**WP1:** To evaluate whether the MCTS is associated with reduced unplanned healthcare utilisation and to examine how outcomes vary by sociodemographic characteristics and service delivery type.

**WP2:** To assess patient-reported outcomes among MCTS users and examine how changes in quality of life, mental health, satisfaction, and wellbeing vary according to sociodemographic characteristics and service delivery models.

**WP3:** To identify and explore the barriers and enablers influencing the effective delivery of the MCTS.

**WP4:** To determine whether the MCTS is cost-effective compared with usual care, and to assess how cost-effectiveness varies by patient characteristics and service delivery type.

### Mersey care telehealth service

The MCTS is a complex, clinician-led remote monitoring intervention designed for patients with long-term conditions and/or an elevated risk of deterioration. The service was initially established in Liverpool in 2011 and delivered through an internally managed Mersey Care platform. In November 2017, following a tripartite partnership between Liverpool Clinical Commissioning Group (CCG), Mersey Care, and Docobo, the service transitioned to the Docobo remote monitoring platform. The service was subsequently expanded to additional localities, including St Helens (September 2021), Sefton (July 2022), Wirral (May 2023), and Cheshire West (February 2024). Across all localities, eligible patients include those with COPD, HF, and diabetes, as well as individuals with any combination of two of these conditions.

The service includes digital or telephone-supported submission of physiological observations and symptom data, asynchronous review by the telehealth team, patient education, self-management support, telephone contact, and escalation to primary, community, specialist, or urgent care services where clinically indicated. Patients may be monitored at varying levels of intensity depending on their condition, risk profile, clinical needs, and care pathway, with monitoring arrangements reviewed regularly by clinical staff. The intervention should therefore be understood as a whole-service model rather than the isolated effect of a digital platform. Consequently, any observed impact on hospital admissions, outpatient activity, or other healthcare utilisation outcomes may reflect the combined effects of technology-enabled monitoring, clinician-led case management, escalation processes, and supported self-management.

Using the Combined Intelligence for Population Health Action (CIPHA) dataset, a regional population health data platform that links routinely collected health and care records (including primary care, hospital, and community data) to support population risk stratification and service planning, patients eligible for the service are identified through established case-finding processes. Patients must be aged 18 years or older, have a confirmed diagnosis, and reside within a commissioned area. Eligibility and case-finding evolved during the study period. Prior to January 2024, identification of potentially eligible patients relied on the Welsh Predictive Model alongside existing clinical caseloads, referral pathways, and clinical judgement. From January 2024, the CIPHA Enhanced Case Finding Tool incorporating the Johns Hopkins Adjusted Clinical Groups (ACG) risk stratification system was introduced. Patients with an estimated six-month risk of emergency hospital admission of 37% or greater may be identified as suitable for telehealth review, subject to clinical assessment and pathway-specific eligibility criteria. As eligibility criteria and case-finding approaches changed over time, the clinical risk profile of patients enrolled in the service may have varied across the study period.

Although the Johns Hopkins ACG risk score (Johns Hopkins University, 2014) is used operationally to support case finding, it is not available for the wider eligible population included in the evaluation dataset and, therefore, cannot be used directly for comparator selection or matching. Consequently, analyses will adjust for available demographic, clinical, socioeconomic, locality, and prior healthcare utilisation characteristics as proxies for baseline risk.

Patients enrolled in MCTS receive a home remote-monitoring package (Doc@Home, Graphnet Ltd), with setup support provided in person, by telephone, or through written guidance. Patients submit daily symptom and physiological readings (e.g., oxygen saturation for COPD and weight and blood pressure for HF) via a mobile app or an NHS-provided device. Monitoring usually happens Monday through Friday for up to 5-months which represents the standard initial monitoring and review period within the telehealth pathway rather than a fixed maximum duration for all patients. Patients may be discharged, extended, stepped down, or re-enrolled according to clinical need and pathway-specific criteria.

MCTS is a complex, clinician-led intervention and variation may occur in monitoring intensity, alert frequency, escalation activity, and staff contact. A team of registered nurses (Band 6–8a) (NHS England, 2024b) and healthcare assistants monitor patient data daily. Alerts are generated using individualised, National Institute for Health and Care Excellence (NICE)-aligned thresholds based on physiological readings, symptoms, or missing data. All alerts are reviewed by the telehealth team and may prompt telephone assessment, self-management advice, referral, or escalation to urgent or emergency care, ensuring a clinician-led rather than fully automated response. Senior clinicians can also set individual thresholds when it makes sense to do so. Healthcare assistants check on patients who do not send in their readings and triage patient calls. Administrative staff support non-clinical activities such as enrolling patients onto the system (Mersey Care NHS Foundation Trust, 2025a; NHS England, 2025c). Patients receive written and video educational resources at enrolment. Patient-reported outcomes, including quality of life, medication adherence, mental health, self-management, and service use, are collected through online questionnaires. Communication is primarily via the app, with telephone contact used when required. Formal fidelity monitoring was not routinely collected; therefore, fidelity will not be formally evaluated. Where available, service activity measures will be reported descriptively to provide context on intervention delivery.

The MCTS was implemented incrementally across localities, conditions and platform configurations. This phased rollout is important for interpreting both service reach and the construction of comparator groups. A map illustrating the phased geographical rollout of MCTS is provided in Table 1 which summarises key changes in geography, eligibility, case finding, commissioned capacity, and platform use over the study period.

**Table 1 TB1:** Timeline of MCTS rollout, eligibility criteria and platform transitions.

Metric	Liverpool	Sefton	St Helens	Wirral	Cheshire West
Monitoring established date^*^	November 2017	July 2022	September 2021	May 2023	February 2024
Eligible conditions	COPD, HF, Diabetes (and any dual combination of these)	COPD, HF, Diabetes (and any dual combination of these)	COPD, HF, Diabetes (and any dual combination of these)	COPD, HF, Diabetes (and any dual combination of these)	COPD, HF, Diabetes (and any dual combination of these)
Monitoring intensities	Full clinical monitoring Light touch monitoring	Full clinical monitoring Light touch monitoring	Full clinical monitoring Light touch monitoring	Full clinical monitoring Light touch monitoring	Full clinical monitoring Light touch monitoring
Referral method (currently)^**^	CIPHA population tool (60%) GP referrals (10%) Step down/light touch (30%)	CIPHA population tool (18%) GP referrals (61%) Step down/light touch (21%)	CIPHA population tool (50%) GP referrals (0%) Step down/light touch (50%)	CIPHA population tool (81%) GP referrals (3%) Step down/light touch (17%)	CIPHA population tool (85%) GP referrals (8%) Step down (8%)
Case-finding approach	QOF conditions = COPD, HF Expanded diagnostic cluster = Type 2 diabetes w/o complication OR Type 2 diabetes w/ complication Age 18+ Nursing home care flag = ‘N’	QOF conditions = COPD, HF Expanded diagnostic cluster = Type 2 diabetes w/o complication OR Type 2 diabetes w/ complication Age 18+ Nursing home care flag = ‘N’	QOF conditions = COPD, HF Expanded diagnostic cluster = Type 2 diabetes w/o complication OR Type 2 diabetes w/ complication Age 18+ Nursing home care flag = ‘N’	QOF conditions = COPD, HF Expanded diagnostic cluster = Type 2 diabetes w/o complication OR Type 2 diabetes w/ complication Age 18+ Nursing home care flag = ‘N’	QOF conditions = COPD, HF Expanded diagnostic cluster = Type 2 diabetes w/o complication OR Type 2 diabetes w/ complication Age 18+ Nursing home care flag = ‘N’
Risk stratification method	Probability of Emergency Admission = 0.37	Probability of Emergency Admission = 0.37	Probability of Emergency Admission = 0.37	Probability of Emergency Admission = 0.37	Probability of Emergency Admission = 0.37
Commissioned capacity	2000	50	100	100	100
Platform used	Docobo (November 2017*—*April 2026) Luscii (April 2026—current)	Docobo (January 2018*—*April 2026) Luscii (April 2026—current)	Docobo (January 2018—April 2026) Luscii (April 2026—current)	Docobo (November 2017—April 2026) Luscii (April 2026—current)	Docobo (January 2018—April 2026) Luscii (April 2026—current)

**Abbreviations:** COPD—Chronic obstructive pulmonary disease; HF—Heart Failure; CIPHA—Combined Intelligence for Population Health Action; QOF—Quality and Outcomes Framework; GP—General Practitioner.

^*^These dates should be interpreted as the time period documented in project documentation for the pathway. However, the true time period where patients enrolled onto the service may be different.

^**^This is based on current patient referral routes as of the 13 July 2026.

## Methods

The methods section of the MCTS evaluation study is organised into four work packages (WPs), which are illustrated in Fig. 1.

**Figure 1 f1:**
[figure not shown]
Methodological framework for the Mersey Care Telehealth Service evaluation study.

**Work package 1:**  *To understand whether the Mersey Care Telehealth Service reduces the use of unplanned health care utilisation and whether there is a differential effect by sociodemographic group and service delivery type*

### Methods

Our primary outcome will be unplanned emergency hospital admissions (outcome 1), secondary outcomes will include: Accident & Emergency (A&E) attendances (outcome 2), 30-day readmission rates (outcome 3), admission to nursing/residential care home (outcome 4), and mortality (outcome 5). The study will analyse the seasonal impacts on hospital admissions during winter.

The study will use quasi-experimental methods and apply two complementary causal approaches: (i) inverse probability of treatment weighted difference-in-differences (IPTW-DiD) (Bettega et al., 2024; Chesnaye et al., 2022; Wei et al., 2023), this is our primary approach to robustly estimate causal effects of telehealth interventions using routinely collected data de-identified by Mersey Care between 2018 and 2024; (ii) To strengthen causal identification, we will also implement regression discontinuity (RD) designs (Thistlethwaite and Campbell, 1960), which are widely adopted in health research (Calonico et al., 2024; Thapa et al., 2025), based on eligibility thresholds derived from the Johns Hopkins ACG risk score (NHS England, 2025d), this is our secondary confirmatory approach. This aspect of the analysis is subject to the availability of Johns Hopkins data. MCTS is commissioned to provide daily care to up to 2,000 patients in Liverpool, 50 patients in Sefton, 100 patients in St Helens, 100 patients in Wirral, and 100 patients in Chesire, respectively. Since the service has not been available over the period to all groups in all parts of Cheshire and Merseyside to construct an appropriate comparator group who did not receive the telehealth service but had similar characteristics (confounders and pre-intervention outcomes) to the patients that did receive it (Barr et al., 2022).

The primary exposure is active enrolment onto the MCTS. Referral alone will not constitute exposure, as not all referred patients commence telehealth monitoring. For enrolled patients, the index date will be defined as the date on which active telehealth monitoring begins. To account for temporal variation in healthcare utilisation and service delivery, telehealth enrolment dates will be grouped into calendar quarters (Q1: January–March; Q2: April–June; Q3: July–September; Q4: October–December). Comparator patients will be selected from quarterly eligibility snapshots comprising individuals who were eligible for MCTS, alive, and registered during the same quarter but who did not enrol onto the service. Calendar quarter will be used as an exact matching variable within the propensity score matching process, ensuring that telehealth participants are compared only with eligible non-enrolled patients observed during the same time period. Additional demographic, clinical, risk, and baseline healthcare utilisation variables will be incorporated into the matching procedure. This approach aims to minimise temporal bias arising from changes in healthcare utilisation, seasonal pressures, COVID-19 recovery effects, admission practices, and service delivery over the study period. The primary analysis will therefore estimate the effect of active enrolment onto MCTS compared with eligible non-enrolment during the same calendar quarter. Findings should be interpreted as representing the effect of the telehealth service model as delivered in routine practice rather than the effect of referral alone or any individual intervention component.

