### Analysis

The study uses two quasi-experimental methods: IPTW-DiD and RD designs. These methods help to reduce the risk of selection bias due to systematic differences between those receiving and not receiving the intervention, in two ways.

The primary approach of the analysis is IPTW-DiD, which is specifically designed to adjust observed differences by reweighting individuals according to their probability of receiving treatment, thereby approximating a pseudo-population in which treatment is independent of observed confounders. The treated cohort will comprise patients who received telehealth, with treatment timing defined by the first quarter in which telehealth was received; patient-quarter observations from this quarter onwards will be considered post-intervention. For untreated patients, comparable index quarters will be assigned to define the pre- and post-intervention periods.

The initial analytic cohort will be restricted to patients aged 50 years or above with at least one relevant long-term condition linked to the telehealth packages: COPD, diabetes, or HF. These eligibility criteria will be applied to both treated and untreated patients to ensure that the control group comprises individuals with a realistic probability of receiving the intervention. To avoid interpreting unobserved quarters as zero healthcare utilisation, the initial analysis will use a balanced panel of patients observed in all 24 quarters across the 6-year study period. The potential selection introduced by excluding patients who die, move away, or register with a GP partway through the study period will be explored in sensitivity analyses.

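### WP1 names difference-in-differences for all five outcomes, but death has no pre-index rate and pre-index care-home admission is depleted by selection, so neither outcome fits a pre/post contrast

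*Protocol article*

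**What the plan says.** The Methods of WP1 list emergency admissions as the primary outcome and four secondary outcomes, ending with "admission to nursing/residential care home (outcome 4), and mortality (outcome 5". The Analysis section of WP1 states: "The primary approach of the analysis is IPTW-DiD". For enrolled patients, "patient-quarter observations from this quarter onwards will be considered post-intervention". For the others, "For untreated patients, comparable index quarters will be assigned to define the pre- and post-intervention periods". Support for parallel trends is to come partly from pre-intervention outcome trends. No outcome is exempted. The only other design named is a regression discontinuity, which depends on data availability.

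Two passages bear on who can have had the event before index:

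- Table 1, in the case-finding row for all five localities, includes "Nursing home care flag = ‘N".
- The WP1 Methods draw comparators from people "eligible for MCTS, alive, and registered during the same quarter but who did not enrol onto the service".

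The WP1 Analysis section describes the cohort differently. It applies age 50 or above and at least one of COPD, diabetes or heart failure to both groups, with no care-home criterion. Table 2 records mortality as a date of death in follow-up and has no row for care-home admission.

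**The concern.** A difference-in-differences subtracts each group's own pre-index rate so that fixed unmeasured differences cancel. This needs a pre-index period in which the event could have happened and been counted. A patient must be alive to start monitoring or to serve as a comparator, so death cannot appear before index. Lasting entry to a nursing home is partly selected out of the enrolled group's history, while those quarters stay in the denominator.

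Two things are at stake. If the groups are screened differently, selection alone can look like an effect of the service. If they are screened alike and completely, the result carries a DiD label but lacks the protection that the label promises. WP4 also counts care and nursing home admission and measures resource use from the WP1 research question, although it does not say that the outcome 4 DiD estimate itself enters the cost model.

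**Working it through.** **No stated figure to reproduce.** The protocol gives no rate, effect size or power for outcomes 4 or 5. Its power statement (relative risk 0.85, 80% power) concerns the primary outcome.

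**Mortality.** Write the rates as pre and post, with E for enrolled and C for comparator.

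- DiD = (post_E − pre_E) − (post_C − pre_C), with pre_E = pre_C = 0 because both groups are alive at index. So DiD = post_E − post_C.
- The ratio form, (post_E/0)/(post_C/0), is undefined.
- The pre-index trend is a flat zero in both groups whatever the confounding.
- The initial balanced panel of 24 quarters also excludes patients who die partway, and the protocol plans sensitivity analyses on that. Lifting the restriction restores post-index deaths but leaves the pre-index zero.

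**Care-home admission.** The following illustrates a service with no effect. Inputs from the protocol: T = 24 quarters and pre/post split at the index quarter. Assumptions, not in the protocol: first admission is absorbing, with the same quarterly hazard h in both groups (0.0025, 0.005 or 0.01); index follows k = 8 to 20 pre-index quarters, uniformly; there is no weighting and no extra mortality after entry.

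Expected events per patient-quarter, averaged over k:

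- Unscreened: pre = [1 − (1−h)^k]/k; post = (1−h)^k × [1 − (1−h)^(T−k)]/(T−k)
- Screened at index: pre = 0; post = [1 − (1−h)^(T−k)]/(T−k)

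Results per 1,000 patient-quarters, with all enrolled patients screened and comparators unscreened:

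| h | Enrolled pre / post | Comparator pre / post | DiD |
|---|---|---|---|
| 0.0025 | 0.00 / 2.47 | 2.46 / 2.39 | 2.47 − (2.39 − 2.46) = +2.54 |
| 0.005 | 0.00 / 4.89 | 4.84 / 4.56 | 4.89 − (4.56 − 4.84) = +5.17 |
| 0.01 | 0.00 / 9.56 | 9.38 / 8.31 | 9.56 − (8.31 − 9.38) = +10.63 |

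The false DiD is linear in the share s of enrolled patients screened. At h = 0.005:

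- s = 0.75: 0.75 × 5.17 = +3.88; ratio form 4.22.
- s = 0.50: 0.50 × 5.17 = +2.59; ratio form (4.72/2.42)/(4.56/4.84) = 2.07.
- s = 0.10: 0.10 × 5.17 = +0.52. Enrolled pre = 0.9 × 4.84 = 4.36 and post = 0.1 × 4.89 + 0.9 × 4.56 = 4.59, so the ratio form is about 1.12.

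In 1,000 simulated studies with an assumed 2,000 enrolled and 10,000 comparators, the false-positive rate was 100% at s = 1. At s = 0.50 it was 75% to 100% across the three hazards, always in the direction of harm.

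If comparators are screened to the same extent, the expected DiD is 0.00 at every h, with a simulated type I error of 4.9% to 6.0%. With complete screening, both pre-index rates are zero. The additive DiD then equals the post-index difference, the ratio is 0/0, and there is no pre-trend to check.

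**The case against.** The strongest reply is that no sentence assigns a model to outcome 4 or 5. Table 2 defines mortality by date of death in follow-up, which suggests a survival analysis, and a SAP that is not shown may specify one. This stands in part: that these outcomes go through the DiD is an inference. But it is drawn from a general statement of method that lists all five outcomes and exempts none, so the text as written fixes a method that does not suit two of them.

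A reader might infer that enrolled patients cannot have had a care-home admission before index. The documents do not support that:

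- The flag names nursing homes, while the outcome includes residential homes, and a temporary stay that had ended could pass it.
- The flag sits under case finding. GP referral and step-down are separate routes, and nothing says that the flag applied to them.
- The protocol says: "From January 2024, the CIPHA Enhanced Case Finding Tool incorporating the Johns Hopkins Adjusted Clinical Groups (ACG) risk stratification system was introduced". It does not say that the flag was used earlier, and the data cover 2018–2024. In a 24-quarter panel ending in Q4 2024, the index quarters modelled here (9 to 21) fall before 2024 except the last.
- The referral shares in Table 1 describe July 2026 and cannot stand in for the share screened in the study data.

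A reader might also infer that a service with no effect will appear to cause care-home admissions. That needs comparators who are not screened in the same way, and the WP1 Methods can be read as screening them. The illustration also leaves out weighting on frailty, living alone and household size. It leaves out the balanced panel too, which could remove some early comparator entrants and shrink the bias. These points limit the size of the bias; they do not create a usable pre-index period.

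**Conclusion.** The point holds in a limited form and is worth correcting before analysis.

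For mortality it needs no assumption beyond being alive at index: the DiD reduces to a post-index comparison, and pre-trends cannot support it. This is not a bias between groups, because both share the zero.

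For care-home admission, pre-index events among enrolled patients are depleted by an unknown amount. Under the cohort criteria in the WP1 Analysis section, selection alone produces a false increase that scales with the share screened, from negligible if few were screened up to about the underlying entry rate if all were. The figures are illustrative because entry rates, group sizes and the share screened are all assumed. If comparators share the screen, as one reading of the WP1 Methods allows, this mechanism gives no bias, but with complete screening the estimate is not a DiD.

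**What to change.** - State in the WP1 Methods and Analysis that IPTW-DiD applies to outcomes that can recur before and after index, such as emergency admissions and A&E attendances.
- Analyse outcomes 4 and 5 as IPTW-weighted time from index, without requiring observation in all 24 quarters.
- For outcome 4, restrict both groups to patients alive and not in a nursing or residential home at index, with death as a competing event.
- Reconcile the comparator definitions in the WP1 Methods and Analysis sections, and say whether the nursing-home flag is part of eligibility. Reconciling alone does not restore a usable pre-index period.
- Add outcome 4 to Table 2 with its definition and data source.
- Report both results as weighted post-index comparisons that do not remove fixed unmeasured differences.

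The cost is some wording and weighted survival models on data sources already listed, such as the Adult Social Care Dataset and primary care. The downside is that these two outcomes lose the DiD label and must be read with more caution about residual confounding.
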